#### Additional analyses

Descriptive analyses at the group level will be conducted on the OPA, ELISPOT and microarray data.

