### What is the optimal schedule for provision of Expanded Program of Immunisation (EPI) vaccines with the incorporation of PCV10?

#### Primary objective

The primary objective is to compare a 2+1 schedule at 2, 4 and 9.5 months of age with a 3+1 schedule at 2, 3, 4 and 9 months of age. The primary hypothesis is that the proportion of participants with protective levels of antibody is non-inferior following a two-dose primary series (arm C) compared with a three-dose primary series (arms A+B). The schedules will also be compared in relation to the geometric mean concentrations (GMCs) of IgG and opsonophagocytosis post-primary series; the proportion of participants with protective levels of antibody, the GMCs of IgG and opsonophagocytosis post-booster; the memory B-cell responses; and the impact on nasopharyngeal (NP) carriage rates and density of bacteria of interest.

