### How do the responses to vaccination with PCV10 or PCV13 compare?

#### Primary objective

The primary objective is to compare a PCV13 schedule at 2, 4 and 9.5 months of age with a PCV10 schedule at 2, 3, 4 and 9 months of age. The primary hypothesis is that the proportion of participants with protective levels of antibody is non-inferior following a two-dose primary series of PCV13 (arm E) compared with a three-dose primary series of PCV10 (arms A+B). The schedules will also be compared in relation to the GMCs of IgG and opsonophagocytosis post-primary series; the proportion of participants with protective levels of antibody, the GMCs of IgG and opsonophagocytosis post-booster; the memory B-cell responses; and the impact on nasopharyngeal (NP) carriage rates and density of bacteria of interest.

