#### Secondary immunogenicity outcome measures

Serotype-specific IgG antibody concentrations for all PCV13 serotypes are measured by ELISA from all blood samples (table 1) and are summarised in terms of both the proportion of children with antibody concentration ≥0.35 µg/mL and the GMC.Opsonisation indices (OIs) for all PCV13 serotypes are measured by opsonophagocytic assay (OPA)^35^ for 100 participants per intervention group (arms A–E) 4 weeks post-primary series and 4 weeks post-booster, and are summarised in terms of the proportion of participants with OI ≥8 and the geometric mean titre.Polysaccharide-specific memory B cells for serotypes 1, 5, 6B, 14, 18C, 19A and 23F are enumerated by ELISPOT^35^ for 50 participants per intervention group (arms A–E) post-booster and at 18 months of age, and for 100 participants per control group (arms F and G) at 18 and 24 months of age. The results are summarised as the median number of antibody-secreting cells.

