### Statistical methods

#### Analysis of primary and secondary outcomes

For each of the two study questions, the primary objective is to compare a 2+1 schedule of (1) PCV10 and (2) PCV13, with a 3+1 schedule of PCV10. The primary outcome is the proportion of participants with serotype-specific antibody concentrations ≥0.35 µg/mL, 4 weeks post-primary series (at 5 months of age). Data from arms A and B are combined to form the three-dose post-primary series group. The primary analyses assess the non-inferiority of (1) two doses of PCV10 at 2 and 4 months of age (arm C) compared with three doses at 2, 3 and 4 months of age (arms A+B); and (2) two doses of PCV13 at 2 and 4 months of age (arm E) compared with three doses of PCV10 at 2, 3 and 4 months of age (arms A+B). The proportion of children achieving protective levels of serotype-specific IgG (≥0.35 µg/mL) 4 weeks post-primary series is determined for each of the 10 PCV10 serotypes. The non-inferiority margin is defined by a 10% difference in absolute risk. The serotype-specific risk differences (arms A+B/arm C) with 90% CIs are calculated using the Newcombe Score method and the null hypothesis rejected if the upper bound of the CI is <10%. Overall non-inferiority is declared if at least 7 of the 10 individual null hypotheses are rejected at a one-sided 5% level of significance. Secondary data analyses to address the primary objective include the ratio of GMCs post-primary series (arm C/arms A+B and arm E/arms A+B) with 95% CIs, and the booster response analysed by analysis of covariance, adjusting for pre-booster levels.

#### Analysis of key secondary objectives for study question 1

A single dose of PCV10 at 2 months of age (arm D) will be assessed for non-inferiority to three doses at 2, 3 and 4 months of age (arms A+B), as described for the primary objective.The impact of a booster dose on pneumococcal and NTHi carriage will be assessed at 12 months of age. Overall pneumococcal, capsular pneumococcal, PCV10 type and NTHi carriage rates will be determined. Proportions will first be compared between the 3+1 group (arm A) and the control group (arm F), using Fisher’s exact test. Where significant differences are found, rates will then be compared between the 3+0 group (arm B) and controls and between the 3+1 and 3+0 groups.

#### Analysis of key secondary objectives for study question 2

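### Both primary objectives promise comparisons of schedules on opsonophagocytosis and memory B cells, but the stated analysis of these assays is descriptive by group, with no between-arm estimate

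*Protocol article*

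**What the plan says.** For study question 1 (optimal PCV10 schedule), the Primary objective section states: "The schedules will also be compared in relation to the geometric mean concentrations (GMCs) of IgG and opsonophagocytosis post-primary series". The list continues with "the GMCs of IgG and opsonophagocytosis post-booster; the memory B-cell responses". The Primary objective section for study question 2 (PCV13 against PCV10) makes the same promise: "The schedules will also be compared in relation to the GMCs of IgG and opsonophagocytosis post-primary series".

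The section Secondary immunogenicity outcome measures defines how each assay is summarised. Opsonisation indices "are summarised in terms of the proportion of participants with OI ≥8 and the geometric mean titre". For memory B cells, "The results are summarised as the median number of antibody-secreting cells". OPA is run in 100 children per intervention arm after the primary series and after the booster. Memory B cells are counted in 50 per intervention arm, post-booster and at 18 months.

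Under Statistical methods, two further between-arm analyses are listed as secondary analyses for the primary objective. One is "the ratio of GMCs post-primary series (arm C/arms A+B and arm E/arms A+B) with 95% CIs". The other, for which no assay is named, is an analysis of covariance of the response to the booster. For the functional and memory assays, the Additional analyses section says: "Descriptive analyses at the group level will be conducted on the OPA, ELISPOT and microarray data".

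**The concern.** The objectives commit the trial to contrasts between randomised schedules. The section that states the method for these assays commits it to something weaker. An analysis plan that follows Additional analyses would give one-arm summaries, from which a reader would have to judge differences between schedules or products by eye. Overlap of two one-arm intervals is a poor guide to the size of a difference or its uncertainty.

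At stake is whether the trial estimates how two doses of PCV10 or PCV13 differ from three doses of PCV10 in functional antibody, and how the boosted schedules differ in functional antibody and memory. The assays are already planned, so the information would be collected but not expressed as a contrast.

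**Working it through.** **The text side by side.** The article states no power, margin or error rate for OPA or ELISPOT, so there is no figure to reproduce. The check is whether any section supplies a between-arm estimate.

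- *Primary objective, both questions:* comparison promised for OPA after the primary series, OPA after the booster, and memory B cells.
- *Secondary immunogenicity outcome measures:* within-group summaries only. This section alone proves little, because IgG is also defined there by group summaries and still receives contrasts later.
- *Analysis of primary and secondary outcomes:* risk differences for IgG, ratios of GMCs, and a booster ANCOVA with no assay named. The outcome section uses GMC for IgG and geometric mean titre for OPA, so the GMC ratio is most naturally IgG. Neither analysis fits memory B cells, which are summarised by medians.
- *Analysis of key secondary objectives, question 2:* arm C against arm E on the IgG threshold only.
- *Additional analyses:* OPA and ELISPOT named, and assigned to group-level description.

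No section gives a between-arm estimate for either assay.

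**Which contrasts the design supports.** The Objectives section pools arms A and B for the post-primary endpoint only, because their primary series is identical. Arm B is 3+0 and receives no booster (Table 1). Both primary objectives name a 3+1 schedule as comparator. So A+B is a valid comparator for post-primary OPA. For post-booster OPA and for memory B cells, measured only post-booster and at 18 months, the 3+1 comparator is arm A alone.

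**Precision available.** Inputs from the article are 100 children per arm for OPA and 50 per arm for B cells. The 200 for A+B takes 100 from each arm. Assumed, because the article does not give them: log10 SD of 0.4, 0.6 or 0.8, and a true proportion with OI ≥8 between 50% and 95%.

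Factor either side of a ratio of geometric means = 10^(1.96 × SD × √(1/n1 + 1/n2)).

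| Comparison | n1 vs n2 | SD 0.4 | SD 0.6 | SD 0.8 |
|---|---|---|---|---|
| Post-primary OPA, C or E vs A+B | 100 vs 200 | 1.25 | 1.39 | 1.56 |
| Post-primary OPA, C vs E; all post-booster OPA contrasts | 100 vs 100 | 1.29 | 1.47 | 1.67 |
| Memory B cells (rough guide only) | 50 vs 50 | 1.43 | 1.72 | 2.06 |

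For example, 100 vs 200 at SD 0.6: 10^(1.96 × 0.6 × √0.015) = 10^0.144 = 1.39. The B-cell row borrows the log scale although the planned summary is a median.

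Half-width for the difference in the proportion with OI ≥8 = 1.96 × √(p(1−p)(1/n1 + 1/n2)).

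| n1 vs n2 | p = 95% | p = 80% | p = 50% |
|---|---|---|---|
| 100 vs 200 | 5.2 points | 9.6 points | 12.0 points |
| 100 vs 100 | 6.0 points | 11.1 points | 13.9 points |

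On these assumptions the OPA contrasts would be informative. Those for memory B cells are feasible but wider.

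**The case against.** **Description may be a deliberate choice.** These are secondary outcomes on subsets chosen by enrolment order, with no hypothesis, margin or power claimed. To compare need not mean to test, and group results shown together are a form of comparison. Part of this stands: description is legitimate, and the absence of a test is no fault. But the article writes explicit between-arm methods for IgG and carriage and a different, descriptive method for these assays, so it draws the distinction itself. If description is the intention, the objectives promise too much.

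**The analysis plan may supply the contrasts.** This is a condensed article, the secondary analyses are introduced as including those listed, and Additional analyses does not say that description is all that will be done. A reader might infer that no between-arm effect will ever be estimated for these outcomes; the article does not go that far. It does state a method for these assays, though, so this is more than a detail left to another document.

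**The GMC ratio or the booster ANCOVA might include OPA.** The objectives can be read as attaching GMCs to opsonophagocytosis as well. That reading is arguable but weak, given the outcome section's terms and the separate placing of OPA under description. It cannot reach memory B cells.

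**More intervals carry a cost.** This stands. OPA gives 13 serotypes × 2 measures × 2 time points × 3 contrasts = 156 intervals. B cells add 7 serotypes × 2 time points × 3 contrasts = 42. The total of 198, unadjusted for multiplicity, calls for a clear non-confirmatory label.

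**Conclusion.** The mismatch is real: comparison is stated under both primary objectives, group-level description is the stated method, and no between-arm estimate appears for OPA or memory B cells. It is worth correcting, but it is confined to secondary outcomes measured on subsets.

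Two stronger inferences should be resisted. First, because these outcomes appear under the primary objectives, a reader might think the primary conclusions are affected. They are not: both primary hypotheses concern the proportion reaching the IgG threshold, and a between-arm analysis is specified for that. Second, a reader might apply the A+B comparator to every outcome. The article supports that pooling only after the primary series; extending it to post-booster OPA or memory B cells would mix boosted and unboosted children in the comparator for a boosted arm.

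The precision figures rest on assumed SDs and proportions, and the 100 vs 200 figures apply to post-primary OPA alone. Even with intervals added, no margin exists for OPA, so the trial would estimate differences in functional antibody without a formal non-inferiority conclusion on them.

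**What to change.** In Additional analyses, add between-arm estimates with 95% CIs for OPA and ELISPOT, labelled secondary and non-confirmatory:

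- **Post-primary OPA, by serotype:** C vs A+B, E vs A+B and C vs E, as the ratio of geometric mean titres and the risk difference in OI ≥8.
- **Post-booster OPA, by serotype:** C vs A, E vs A and C vs E, with the same two measures. Arm A alone is the 3+1 comparator.
- **Memory B cells, post-booster and at 18 months, by serotype:** C vs A, E vs A and C vs E, as a Hodges-Lehmann location shift. Describe it as a shift, not as a difference in medians, and note the lower precision at 50 per arm.

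The C vs E contrast serves the key secondary objective of comparing the two products in the 2+1 schedule.

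The cost is a short paragraph of analysis text and up to 198 unadjusted intervals, which probably belong in supplementary tables. No new samples, assays or participants are needed.

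Alternatively, if only description is intended, reword the Primary objective sections of both study questions so that opsonophagocytosis and memory B cells are described by group rather than compared. That costs one sentence in each.

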#### Populations of analysis

Analyses will be on a per-protocol population. The primary non-inferiority analyses will be repeated on an intention-to-treat population (ITT), with all participants analysed in the group they were randomised to. Any differences between the per-protocol and ITT analyses will be reported. For each outcome, all available data will contribute to the analyses. To investigate whether data are missing completely at random, we will explore whether attrition varies across the study arms based on baseline covariates. If differential attrition is dependent on baseline variables, we will use a modelling approach to adjust for any such baseline factors and we will present the adjusted results along with the primary analysis.

#### Additional populations of analysis

OPAs will be conducted on a subset of 100 participants per group. The first 100 participants per group with both post-primary series and post-booster blood samples available will contribute to the OPA analysis.B-cell assays will be conducted on a subset of 50 participants per group for arms A–E and 100 participants per group for arms F and G. The last 50/100 participants enrolled per group will have blood samples collected for the B-cell analysis.

### Data monitoring

Data monitoring committee: Safety oversight is under the direction of an independent Data Safety and Monitoring Board (DSMB), in accordance with a DSMB Charter kept in the trial office. The DSMB will meet approximately three times a year to review aggregate and individual participant data related to safety, data integrity and overall conduct of the trial, including a detailed review of all serious adverse events (SAEs).

Interim analyses and stopping guidelines: No interim analyses are planned. Stopping guidelines are based on safety. An extraordinary meeting of the DSMB will be called in the event that serious safety issues emerge, to provide recommendations regarding termination of the trial. A final decision to terminate rests with the Principal Investigators and the Sponsor.

### Harms

Data on SAEs will be collected throughout the study, with parents asked about hospitalisations and significant signs and symptoms at each study visit and through a regular review of hospital records. Details of any SAEs will be recorded on the standard reporting form from the Vietnam Ministry of Health and reported to the Principal Investigators and the Ethics Committees. Participants will be kept under observation for 30 min following vaccine administration to monitor for any adverse reactions, and information on reactogenicity in the 72 hours following vaccine administration will be recorded on parent held diary cards.

### Auditing

External site monitoring will be provided by FHI360, to independently assess protocol and good clinical practice (GCP) compliance. Monitoring visits will occur at study initiation, close-out and approximately twice a year in each study clinic. 100% of Informed Consent Forms and SAEs and a random selection of approximately 20% of participant folders will be monitored, along with the Trial Regulatory File and laboratory records.

### Patient and public involvement

Patients were not involved in the development, design, recruitment or conduct of the study. Community consultation took place at the district level during the design phase, as well as discussion and approval of the design from the district and city level Ministry of Health and the People’s Committee of Ho Chi Minh City. Participants will be informed of the overall study results by post, with a postal address collected at the final study visit.

## Ethics and dissemination

### Research ethics approval

The protocol, the Plain Language Statement (PLS) and the Informed Consent Form (ICF) have approval from the Institutional Review Board at the Pasteur Institute of Ho Chi Minh City, the Vietnam Ministry of Health Ethical Review Committee and the Human Research Ethics Committee of the Northern Territory Department of Health and the Menzies School of Health Research. Both Ethics Committees receive annual reports on the trial progress, for continuing approval of the trial.

### Protocol amendments

Any modifications to the protocol that may impact on the conduct of the study will be documented in a formal protocol amendment and approved by both Ethics Committees prior to implementation of the changes. The modified protocol will be given a new version number and date. The Ethics Committees will also be notified of any minor corrections/clarifications or administrative changes to the protocol, which will be documented in a protocol amendment letter. Significant protocol changes will also be updated in the ClinicalTrials.gov record.

### Consent

#### Obtaining consent

The consent process is undertaken by specifically trained study staff. The study staff will go through the PLS and ICF, translated into Vietnamese, in detail with the potential participant’s parent/legal guardian. The study staff will then discuss the trial further and answer any questions that may arise. Written informed consent is required prior to enrolment of the infant into the study. Consent is obtained from the parent/legal guardian as the participants are too young to provide consent themselves. A copy of the PLS and ICF will be given to the parent/legal guardian for their records.

#### Ancillary studies

Specific consent for the indefinite storage of blood and NP samples for future research related to the trial will be obtained from the parent/legal guardian and recorded on the ICF. Any future research will undergo ethical review. Any samples for which indefinite storage is not consented to will be destroyed at the close of the trial.

### Confidentiality

All study-related information will be stored securely and held in strict confidence. All documents kept at the study clinics, including the ICFs and participant folders, are stored in locked cabinets. All documents kept centrally are stored in the trial office, which is kept locked. Electronic data is stored in the trial office and on a secure password protected server. The electronic data and laboratory samples are coded by a unique participant number and do not contain the participant name. Access to participants’ information will be granted to FHI360 for monitoring purposes, and to the Ethics Committees or DSMB if required.

### Access to data

The final trial dataset will be under the custody of the trial sponsor, Murdoch Children’s Research Institute (MCRI). The Principal Investigator, trial manager and trial statistician will have access to the full anonymised final dataset.

### Ancillary and post-trial care

Participants are advised to come to the study clinic for ancillary care, or to Children’s Hospital Number 2 in Ho Chi Minh City, where they will not be charged for treatment and services. All participants are covered by clinical trials insurance for trial related harms.

### Dissemination policy

#### Plans

Participants will be informed of the overall study results by post, with a postal address collected at the final study visit. Following completion of the trial, the results will be submitted for publication in peer-reviewed journals, and presented at relevant international conferences. Agreements between MCRI and each of the Pasteur Institute of Ho Chi Minh City and GSK Biologicals SA provide that a party must obtain the prior approval of the other parties in advance of submitting a manuscript for publication, and that such approval will not be unreasonably withheld.

#### Authorship

A publication subcommittee will consider all proposed publications, with the final decision on content and authorship resting with the Principal Investigator. The role of each author will be published. Group authors may be used where appropriate. There are no plans for the use of professional writers.

#### Reproducible research

There are no plans to grant public access to the full protocol, participant-level dataset or statistical code.
